### Follow-up and compliance to the study

To improve the follow-up rate, at the beginning of the study participants will be informed of the importance to attend all sessions, and the staff will register name and

contact information for follow-up on missed sessions to collect information on the reasons for the absence, and to offer women the opportunity to attend the session on a different day and/or time as soon as possible. Door-to-door transportation and a kit, containing a t-shirt, running tights and running shoes, will be offered for women in the intervention group. Both groups will be given study t-shirts and laboratory results around 10 days after collection. To be considered adherent to the intervention, women should attend 16 weeks of the program and a minimum of 34 (70 %) workout sessions, and cannot miss more than six training sessions in a row.

### Control group

Women allocated to the control group will be instructed to continue their usual routines, will do the same assessments as the intervention group and will be followed by the 2015 Pelotas (Brazil) Birth Cohort Study.

### Sample size calculation

For the sample size calculation, based on a statistical power of 80 %, a level of significance set at 5 % and using different outcomes from the last birth cohort [28] and estimates based on secular trends (preterm birth at 16 %, gestational hypertension at 18 %, leisure-time physical activity during pregnancy at 13 % and estimate of risk reduction with the intervention at 30 %), we estimated that 213 women would be necessary for the intervention group. The intervention:control ratio will be 1:2, therefore 426 will be included as the control group.

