## Background

The World Health Organization estimates that over 10 % of births worldwide are preterm [1]. Based on previous population studies in the city of Pelotas (Brazil), the preterm birth rate is increasing (from 6.3 to 14.7 % between 1982 and 2004) [2]. Preterm birth is associated with most cases of neonatal deaths and negative consequences throughout childhood and adult life [3, 4].

Among the strongest predictors of preterm birth are hypertensive disorders of pregnancy [5–7]. Evidence suggests that preterm birth and gestational hypertension risk may be altered by regular leisure-time physical activity [8–12]. The potential hypothesis for such a mechanism is based on reduction in blood pressure, improvement in blood lipids profile, reduced oxidative stress and inflammation reduction [13–15]. Studies also have shown that leisure-time physical activity during pregnancy is associated with lower risk of excessive weight gain [16] and better psychological health [17, 18]. Although evidence supports the benefits of physical activity during pregnancy, few women in Brazil are active during gestation, and the level of leisure-time activity decreases as pregnancy advances [19]. Further, the effect of physical activity on mother-child health outcomes is not fully understood.

With respect to different outcomes, such as diabetes, trials during pregnancy do not provide enough evidence that exercise is effective [20]. The main goal of conducting a trial in the Brazilian population is because physical activity among Brazilian women is highly associated with socioeconomic status and other characteristics not easily controlled statistically during analysis. This trial will allow for the balance of such potential confounders, as we are using a population-based sample and random allocation. Moreover, few experimental studies have been carried out to study such associations in large samples.

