### Randomization

Pregnant women meeting the inclusion criteria and who agree to participate in the randomized controlled trial will be allocated randomly into either the intervention or control group. The randomization process will be done in blocks of nine women using random software sampling. Each block will therefore result in the allocation of three women for the intervention and six women for the control group, ensuring a recruitment balance of 1:2 throughout the study. This ratio was chosen as it would minimize costs and behavioral changes in women from the remaining cohort, whilst assuring that statistical power would be unaffected. As the cohort is an observational study, our option was to expose the lowest possible number of women to the intervention. After randomization, women will be allocated into either one of these groups: control, 426 women who will keep their usual daily activities; and intervention, 213 women who will engage in a physical activity program, three sessions a week.

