### Primary outcome measures

Preterm birth (gestational age below 37 weeks of pregnancy), and pre-eclampsia (blood pressures above 140/90 mmHg and proteinuria above 15.0 mg/dL) will be assessed during pregnancy and soon after birth.

[figure not shown]

**Fig. 1** Study design

**Table 1** Exclusion criteria of the randomized controlled trial

| Exclusion criteria            | Description                                                   |
|-------------------------------|---------------------------------------------------------------|
| Age                           | Below 18 years                                                |
| Hypertension                  | Diagnosed before pregnancy/Self-reported                      |
| Diabetes                      | Diagnosed before pregnancy/Self-reported                      |
| Preterm birth                 | History of previous preterm birth                             |
| Miscarriage                   | History of previous miscarriage                               |
| Heart disease                 | Diagnosed before pregnancy/Self-reported                      |
| In vitro fertilization | Fertilization in the current pregnancy                        |
| Double/twin pregnancy         | Twin pregnancies confirmed by ultrasound                      |
| Persistent bleeding           | Women presenting persistent bleeding                          |
| Severe obesity                | Body mass index above 35 kg/m                     |
| Heavy smokers                 | Smoking more than 20 cigarettes a day                         |
| Active women                  | Weekly leisure-time physical activity > 150 min/Self-reported |

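### The stated 80% power does not follow from the protocol's own inputs (213 and 426 women give about 36% for preterm birth), and unadjusted cohort rates and no loss allowance probably lower it further

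*Protocol*

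**What the plan says.** The protocol's Sample size calculation is "based on a statistical power of 80 %, a level of significance set at 5" per cent. It draws its rates from the previous cohort and from trends, "using different outcomes from the last birth cohort [28] and estimates based on secular trends", and gives "preterm birth at 16 %, gestational hypertension at 18" per cent. It assumes a 30% risk reduction and concludes that 213 intervention women are needed, with 426 controls at 1:2. No restriction of the rates to trial-eligible women is mentioned.

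The Randomization section uses the same numbers as the numbers to be allocated: "intervention, 213 women who will engage in a physical activity program, three sessions a week", and 426 controls. The numbers needed and the numbers randomised are therefore identical, with nothing added for loss.

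Table 1, under Primary outcome measures, excludes women with "History of previous preterm birth" and women with twin pregnancies, among other conditions. It also excludes women who already do more than 150 minutes of leisure-time activity a week. The primary outcomes in that section are preterm birth and pre-eclampsia. Gestational hypertension is not one of them, and pre-eclampsia has no planning rate.

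**The concern.** The sample size is the protocol's only statement of what the trial can detect on its primary outcomes. If the stated power is far too high, a null result on preterm birth could be read as evidence of no effect when the trial had little chance of showing one.

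There are two layers. The first is arithmetic: the stated numbers can be checked directly against the stated inputs. The second concerns the inputs. A rate for all women in a cohort is likely to be too high for a trial that removes women with a previous preterm birth and twin pregnancies, and any lost outcome reduces the number analysed below the number said to be necessary. Correcting only the arithmetic would leave a restated power that still rests on unadjusted inputs.

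**Working it through.** **Inputs from the protocol.** Control rate p = 0.16 (preterm birth) or 0.18 (gestational hypertension); 30% relative reduction, so q = 0.7p = 0.112 or 0.126; power 80%; significance 5%; n = 213 intervention and 2n = 426 control. Sidedness is not stated; two-sided is taken here.

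**Formula** (pooled normal approximation, 1:2 allocation). With p̄ = (q + 2p)/3, s0 = √[1.5·p̄(1 − p̄)] and s1 = √[q(1 − q) + p(1 − p)/2]:

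- intervention n = [(1.960·s0 + 0.842·s1)/(p − q)]²
- power = Φ{[√n·(p − q) − 1.960·s0]/s1}

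**Step 1: the plan's own figure.**

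- Preterm birth: p̄ = 0.144, s0 = 0.430, s1 = 0.408, difference 0.048. Required n = 611 (with 1222 controls). At n = 213, power = Φ[(0.7005 − 0.8428)/0.4082] = Φ(−0.348) = 36.4%.
- Gestational hypertension: p̄ = 0.162, s0 = 0.451, s1 = 0.429, difference 0.054. Required n = 532 (with 1064 controls). At n = 213, power = Φ[(0.7881 − 0.8844)/0.4289] = Φ(−0.225) = 41.1%.

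The stated 213 is not reproduced.

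**Step 2: other conventions.** Intervention-arm n for 80% power:

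| Variant | 16% | 18% |
|---|---|---|
| Two-sided, pooled | 611 | 532 |
| With continuity correction | 642 | 560 |
| Unpooled variance | 568 | 496 |
| One-sided | 480 | 418 |
| 30% read as an odds reduction | 797 | 720 |
| Women split 13:87, one-sided | 374 | 325 |

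The last row uses the protocol's 13% for leisure-time activity as an exposure share. None of these gives 213. One-sided power at 213 and 426 is 49.3% and 54.3%.

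**Step 3: what 213 and 426 can detect.** Two-sided 80% power requires a risk ratio of about 0.514 at 16% (16% to 8.2%) or 0.543 at 18% (18% to 9.8%), that is, reductions of about 49% and 46%. With a 30% reduction, the control rate would have to be about 36%. That exceeds even the sum of the two planning rates, 34%, at which power would be 76%; in any case the protocol defines no composite outcome.

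**Step 4: rates in eligible women and loss.** The documents give neither a rate for eligible women nor a loss figure. The values below are assumptions, for preterm birth with a 30% reduction at 213 and 426:

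| Assumed control rate | Assumed loss | Power | Intervention n for 80% (before loss) |
|---|---|---|---|
| 16% | 0 | 36.4% | 611 |
| 16% | 10% | about 33% | 611 |
| 14% | 0 | 31.7% | 713 |
| 12% | 0 | 27.1% | 848 |
| 10% | 0 | 22.6% | 1038 |

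**Step 5: the share of each layer.** The plan's own inputs take power from 80% to 36%, a fall of about 44 points. From there, a 14% rate costs about 5 points, a 10% rate about 14, and 10% loss about 3. In a correctly sized design (611 and 1222), a true rate of 12% would lower power from 80% to 65.6%, 10% loss alone would lower it to 75.6%, and both together to 60.8%. The second layer is therefore worth correcting even after the first is put right.

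**The case against.** The strongest objection is that the documents do not show the 16% to be inflated. The cited cohort report is not visible, so any restriction in it is unknown. The Background gives 6.3% preterm births in 1982 and 14.7% in 2004; a straight line reaches 14.7 + (8.4/22) × 11 = 18.9% in 2015, so 16% lies below trend. Excluding already active women may raise the control rate on the protocol's own hypothesis. This stands as a limit on size: the direction is probable, but the amount is unknown. It does not touch Step 1, and the trend line is a whole-population rate that says nothing about women without previous preterm birth or twins.

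Loss may also be small. Preterm birth comes from the perinatal study information, collected at a hospital interview soon after birth, and the host cohort follows the controls. That is fair, and the 10% is only an illustration.

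Four stronger readings are tempting but not supported:

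- A reader might infer that the exclusions and missing loss allowance explain the shortfall from 80%. They do not; the stated inputs alone produce most of it.
- A reader might combine the Background's statement "Among the strongest predictors of preterm birth are hypertensive disorders of pregnancy" with the hypertension exclusion in Table 1 and conclude that this predictor has been removed. The statement concerns disorders arising in pregnancy, whereas Table 1 excludes hypertension diagnosed before pregnancy.
- A reader might infer an expected adherence of 70% and dilute the effect accordingly. The 70% is a session threshold for each woman, not an expected share of adherent women, and the protocol does not say whether its 30% already is an intention-to-treat effect.
- A reader might suspect that an arm size was divided as if it were a total, since the continuity-corrected 642 is near 213 + 426 = 639. Nothing in the document confirms this.

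**Conclusion.** The concern holds in two parts of unequal strength. The firm part is that 213 and 426 women do not give 80% power under the protocol's stated inputs. Taking two-sided 5% and a relative reduction of 30%, power is about 36% for preterm birth, and no convention tried recovers 213. The 41% for gestational hypertension offers no cover, because that is not a primary outcome.

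The probable part is that power for preterm birth is lower still, because the 16% carries no stated restriction to eligible women and no loss is allowed for. The documents cannot size this. The illustrative range of roughly 23% to 33% rests on assumed control rates of 10% to 14%, or on an assumed 10% loss at 16%.

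**What to change.** Revise the Sample size calculation as follows:

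1. Re-estimate the preterm control rate in the previous cohort after applying those Table 1 exclusions that it recorded, and list any that could not be applied. The earlier cohorts enrolled at birth, so some items may be missing.
2. State a loss allowance for preterm birth, even if it is near zero because the outcome is recorded at delivery.
3. State the sidedness of the test, and whether the 30% is the effect expected under intention to treat.
4. Restate the power, or the detectable reduction, for preterm birth at 213 and 426. On the present 16% with no loss these are about 36% and about 49%.
5. Do not rest the power statement on gestational hypertension.

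The cost is a tabulation of existing cohort data, a short recalculation and revised wording. The price is a much less favourable power figure. No change to the conduct of the trial is needed to report it.

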### Statistical analysis

Statistical analyses will be conducted on an intention-to-treat basis, but secondary analyses will be performed, including only those considered adherent to the protocol. Baseline characteristics will be presented using descriptive statistics to compare both groups.

According to the type and distribution of variables, between-groups differences will be evaluated using adequate tests. Continuous variables will be analyzed by t tests (for symmetrically distributed data), or Mann-Whitney U tests (for asymmetrical data). Categorical

[figure not shown]

**Table 2** Stages of training routines during pregnancy according to week of intervention

| Weeks of intervention | Warm-up | Aerobic exercise | Strength training/Floor exercises | Stretching |
|-----------------------|---------|------------------|-----------------------------------|------------|
| 1 to 4, Stage 1       | 5 min   | 15 min           | 35 min (sets: 3 × 12 repetitions) | 5 min      |
| 5 to 10, Stage 2      | 5 min   | 20 min           | 30 min (sets: 3 × 10 repetitions) | 5 min      |
| 11 to end, Stage 3    | 5 min   | 25 min           | 25 min (sets: 3 × 8 repetitions)  | 5 min      |

variables will be analyzed with chi-square tests or Fisher's exact test, as appropriate. General linear model or logistic regression will be employed to control for confounding factors. More specifically, based on the perinatal study information, preterm birth, gestational diabetes and eclampsia incidences will be compared in the two groups using chi-square tests, followed by multivariable analyses when adequate; linear regressions will be carried out to evaluate potential differences in birth weight, gestational weight gain and lipid profile. Analysis will be carried out in the statistical package STATA 12.0 (StataCorp, [name]) and significance will be set at 5 %.

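### The stated sample size of 213 versus 426 does not follow from its own inputs: for a 30% relative reduction it gives about 36% power for preterm birth, not 80%

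*Protocol*

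**What the plan says.** The Protocol's Sample size calculation section says the size is "based on a statistical power of 80 %, a level of significance set at 5" per cent. It lists outcome rates from an earlier cohort and secular trends, "preterm birth at 16 %, gestational hypertension at 18" per cent, together with "leisure-time physical activity during pregnancy at 13" per cent. It closes with "estimate of risk reduction with the intervention at 30 %), we estimated that 213 women would be necessary for the intervention group", and derives 426 controls from a 1:2 ratio. The Abstract and the Randomization section repeat 213 and 426.

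The section gives no formula, no sidedness, no dropout allowance and no role for the 13% activity figure. It does not say which outcome drives the 213. The Statistical analysis section plans chi-square tests for the categorical outcomes at 5%. The Primary outcome measures section names preterm birth and pre-eclampsia. Gestational hypertension, which appears in the calculation, is not among them.

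**The concern.** A two-proportion calculation at rates near 16% to 18%, with a risk ratio of 0.70 and 80% power, normally needs well over a thousand women. A total of 639 looks far too small. If it is, the Protocol tells readers that the trial would probably detect the hypothesised effect when it probably would not, outcome by outcome. A null result for preterm birth would then be read as evidence that exercise does not prevent it. The Discussion makes this more pressing: it counts the large sample among the study's strengths and foresees use of the results in routine prenatal counselling.

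**Working it through.** **Inputs (Sample size calculation section).** Power 80%; significance 5%; control risk 16% or 18%; risk reduction 30%; intervention:control 1:2; 213 + 426 = 639 women.

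**Assumptions.** The test is two-sided (sidedness is not stated; one-sided results are also given). The 30% is relative, because 30 percentage points cannot be taken from 16% or 18%. The intervention risks are then 0.70 × 16% = 11.2% and 0.70 × 18% = 12.6%.

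**Attempt to reproduce 213.** With pI and pC the intervention and control risks, and p̄ = (pI + 2pC)/3, the pooled-variance formula for 1:2 is

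n(intervention) = [1.960 × √(1.5 p̄(1 − p̄)) + 0.842 × √(pI(1 − pI) + pC(1 − pC)/2)]² / (pC − pI)²

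- Preterm birth: p̄ = 0.144, and the roots are 0.4300 and 0.4082. n = (1.1864 / 0.048)² ≈ 611, with 1,222 controls.
- Gestational hypertension: p̄ = 0.162, and the roots are 0.4513 and 0.4289. n = (1.2454 / 0.054)² ≈ 532, with 1,064 controls.

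**Other readings, intervention-arm n.**

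| Reading | 16% | 18% |
|---|---|---|
| Two-sided | 611 | 532 |
| Two-sided, continuity correction | 642 | 560 |
| One-sided | 480 | 418 |
| Odds ratio 0.70 instead of risk ratio | 797 | 720 |
| Stated rate taken as the intervention rate | 398 | 343 |
| 13:87 exposure ratio instead of 1:2 | 478 | 416 |

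Taking 13% as the outcome rate gives 775. A composite of the two outcomes, which the Protocol does not plan, gives 266 if they are independent (31.1%). If the rates are simply added (34%), it gives 235 two-sided or 185 one-sided. None of these is 213. With a 30% reduction, 213 would need a control risk of about 36%. A dropout allowance would raise n, so it cannot explain a shortfall.

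**Power at 213 versus 426.** Power = Φ[((pC − pI) − 1.960 × SE0) / SE1], with SE0 pooled and SE1 unpooled.

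- Preterm birth: (0.048 − 1.960 × 0.02946) / 0.02797 = −0.348, so power is 36.4%.
- Gestational hypertension: (0.054 − 1.960 × 0.03092) / 0.02939 = −0.225, so power is 41.1%.

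Simulating the chi-square test 400,000 times gives 36.7% and 41.6%. One-sided, the formula gives 49.3% and 54.3%. One-sided with unpooled variance gives about 53% and 58%.

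**Detectable effect.** Two-sided power reaches 80% at a risk ratio of about 0.51 for preterm birth (16% to 8.2%, a 49% reduction), or about 0.54 for gestational hypertension (18% to 9.8%, a 46% reduction).

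**If the planned effect is observed exactly (preterm birth).** The standard error of the log risk ratio is √(0.888/23.86 + 0.84/68.16) = 0.2226. The 95% interval is 0.70 × exp(±1.960 × 0.2226) = 0.45 to 1.08, which includes 1.

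**The case against.** The fair reply is that the section leaves several inputs open (sidedness, formula, driving outcome, use of the 13%) and rests on a cited source not at hand. The defensible statement is therefore that 213 cannot be reproduced from the stated inputs under any variant tried, with the two-sided test and the relative scale labelled as assumptions. That affects the wording, not the conclusion: one-sided testing still leaves power near one half.

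A reader might infer more than the document supports on four counts.

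- **That the ratio statement is false.** The Randomization section says 1:2 was chosen "whilst assuring that statistical power would be unaffected". At a fixed 639 women, 1:1 would give more power (about 42% and 47%). But the Protocol fixes no total. It aims to expose as few women as possible to the intervention and derives that arm first. With 213 treated, going from 213 to 426 controls raises power from about 30% to 36% at 16%, and from about 34% to 41% at 18%. The ratio is a legitimate choice; the error lies in the sample size calculation.
- **That the trial as a whole would usually be non-significant.** If both effects existed as assumed and the outcomes were independent, the chance of at least one significant result would be 1 − 0.636 × 0.589 ≈ 63%. The more-often-than-not statement holds for each outcome separately.
- **That 41% is the power for the second primary outcome.** That outcome is pre-eclampsia. No rate is given for it, so its power cannot be computed.
- **That the cause is known.** The total of 639 is close to 642, the continuity-corrected intervention-arm number for preterm birth. A per-arm figure may have been split as a total, but nothing in the Protocol confirms this.

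**Conclusion.** The point holds for the sample size statement. The required intervention arm is about 2.9 times the stated number for preterm birth (611/213) and 2.5 times for gestational hypertension (532/213). The stated 80% power is about 36% and 41%, assuming a two-sided 5% test, a relative 30% reduction and the stated rates as control risks; one-sided testing gives 49% and 54%. Only the preterm birth figure bears on a named primary outcome. Because the inputs, the power and the resulting number are all fixed in the Protocol, an analysis plan could not make 213 follow from them. It must be corrected before a null result is interpreted. The conclusion does not extend to the allocation ratio or to the trial's overall chance of a significant finding.

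**What to change.** Rewrite the Sample size calculation section to state:

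- that the test is two-sided (or one-sided, if that was intended) and that the 30% is a relative reduction;
- that 213 versus 426 gives about 36% power for a 30% reduction in preterm birth from 16%, and about 41% for gestational hypertension from 18%;
- that 80% power is reached only for reductions of about 49% and 46% respectively;
- that gestational hypertension is not a primary outcome, and that power for pre-eclampsia is not established without an assumed rate;
- what part, if any, the 13% activity figure plays;
- that a non-significant result does not exclude the planned 30% reduction.

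The sentence on the 1:2 ratio can stay. Giving the risk ratio with its 95% confidence interval as the headline result would help readers, but it is an optional reporting choice and not part of this correction.

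The cost is wording only. No additional women and no change in conduct are needed, although the declared power becomes much less favourable.
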